#### Data management

##### Data forms and data entry

In the PELYCAN trial, all data will be entered electronically in case report forms (eCRFs). This will be done at the Department of Urology at the University Medical Center Mannheim. Personal information about potential and enrolled participants will be collected, shared, and maintained with third-party only after pseudonymization in order to protect confidentiality. All demographic and baseline clinical data, as well as primary and secondary outcome measures, will be recorded in the eCRF. Original study forms (e.g., those who will be sent to the patients for follow-up either electronically or by post) will be entered and kept on file at the department. Data management will be done by [name] and the study center of the department of urology and urologic surgery.

##### Data transmission and editing

To promote data integrity, a variety of mechanisms will be used. Referential data rules, valid values, range checks, and consistency checks against data already stored in the database will be supported. The option to choose a value from a list of valid codes or options will be available where applicable. Checks will be applied at the time of data entry into a specific field.

##### Storage, security, and back-up of data

Data will be stored in compliance with data protection regulations. Access to the study data will be restricted. All forms related to the study will be kept in locked cabinets. The electronic data forms will be password-protected. These passwords will be changed on a regular basis. All reports will be prepared such that no individual subject can be identified by using the patients “hospital-ID.” A complete back-up of the primary database will be performed twice monthly. These back-ups will be stored off-site. A complete back-up of the primary database will be retained indefinitely.

### Statistical methods

#### Outcomes

The intervention arm (PELYCAN) will be compared against the control for all primary analyses. The primary analysis will be based on the intention-to-treat (ITT) principle. In addition, per protocol (PP) and as-treated (AT) analyses will be performed as sensitivity analysis. We will use chi-squared test for binary outcomes and *t* test for continuous outcomes. Categorical data will be reported with absolute and relative frequencies. Continuous outcomes will be reported with mean/median as well as standard deviation and (interquartile)-range. For subgroup analysis, we will use regression methods. Multivariable analyses will be based on logistic regression for binary outcomes and linear regression for continuous. *P* values will be reported to four decimal places with *p* values less than 0.001 reported as *p* < 0.001. Up-to-date versions of SPSS (Chicago, IL) and R will be used to conduct analyses. For the primary outcome, the *p* value will be adjusted according to the adaptive design in order to avoid a type I error. All other analyses will be exploratory with 2-sided *p* values of alpha < 0.05 and a power of 80%. Statistical analysis will be performed by a statistician who is otherwise not involved in the conduct of the study.

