#### Concomitant care

To us, there is no known concomitant care or intervention, which could possibly affect the outcome in terms of a cointervention bias. All patients receive the same pre-, peri- and postoperative care according to local standard operating procedures.

A difference exists in postoperative anticoagulation therapy depending on pre-existing medical conditions. Some patients are in need of therapeutic anticoagulatory whereas all others will receive a low molecular weight heparin for thrombosis prophylaxis for 4 weeks postoperatively as standard of care according to current guideline recommendations. Hence, we will stratify for therapeutic or prophylactic anticoagulatory therapy.

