#### Sample size

The sample size was calculated on the basis of the primary hypothesis. The incidence of symptomatic lymphoceles after RARP has been listed with 2–15% [6], 0–8% [17], and 9–51% [31, 36]. The incidence of post-prostatectomy *lymphoceles in general* has been described with an occurrence of 10–18%, [1], 30% [17], and up to 61% [37]. The previously conducted studies on PF for lymphocele prevention list the incidences for *symptomatic lymphoceles* in their control groups with 4.6% [16], 11.6 [6], 4.1% [17], 9,1% [20], and 9.7% [20], respectively. Stolzenburg et al. have been describing 8.3% *asymptomatic lymphoceles* in their matched-pair cohort; Bründl et al. described an incidence of asymptomatic lymphocele in 24.2% in the control group within the first 90 days postoperatively [16, 20].

Therefore, we assume a rate of symptomatic lymphoceles of 10% for the control group which can be reduced to 2% for the PELYCAN group. Using a power of 80% and a one-sided α (type 1 error) level of 0.025, we calculated a sample size of *n* = 141 per arm, in total *n* = 282. Assuming a drop-out rate of approximately 6%, we aim for a study population of 300 patients. However, due to uncertainty in the actual incidence of symptomatic lymphoceles and the effect of the intervention, sample size recalculation will be performed after an interim analysis in an adaptive study design after completion of the follow-up of the first 120 patients. According to the results of the sample size recalculation, the trial might be terminated for futility or efficacy by the PI or the sample size will be adapted [38, 39]. The maximum number of patients will be 1000.

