#### Randomization

Eligible patients will be stratified for lymphocele risk factors and operating surgeon. Hereafter, randomization will be performed as block randomization with a 1:1 allocation to either using a PF (PELYCAN) or standard procedure without a PF (control). Block sizes will be kept confidential until study completion. Randomization and allocation will take place the day before surgery with a web-based computer algorithm (uroservy.de), which was specially developed for this study by the Heinrich-Lanz Center for Digital Health, Medical Faculty Mannheim, University of Heidelberg.

Randomization will be stratified for possible risk factors for lymphocele formation and the surgeon performing the procedure. The process of stratification is included in the “randomization process”: Patients are stratified for anticoagulation therapy (yes vs. no), extended lymphadenectomy (yes vs. no), diabetes mellitus (yes vs. no), and the surgeon performing the procedure. These categories have to be answered during the randomization process. Following this stratified proportionate sampling combined with randomization, we aim to ensure an equal allocation of participants to each experimental condition (intervention vs. non-intervention). That is done to control for the possible confounding variables regarding postoperative lymphocele formation (e.g., preventing that significantly more patients with extended LAD are randomized into the non-intervention group). Stratification based on intraoperative patient characteristics was considered impossible. To avoid over-stratification, we limited the number of strata. Aiming for a high number of patients, blocking within the strata will be performed. All patients included will be used for statistical analyses.

The randomization and allocation process will be performed by a person, who is completely uninvolved in the running of the trial, the study inclusion, the process of taking the patients’ consent, the operation or postoperative assessment of lymphoceles. This person cannot be influenced by people involved in the trial.

All randomized study participants will stay included in the trial. Follow-up information will be collected in order to prevent missing data.

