#### Additional analyses

We plan to conduct subgroup analyses with strong biological rationale and possible interaction effect. The subgroup analysis will compare odds ratios for the use of titanium clips during lymphadenectomy versus lymphadenectomy without the use of clips.

A sensitivity analysis of the primary endpoint will adjust for the pre-randomization variables which might reasonably be expected to be predictive of outcomes.

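### The primary chi-squared test ignores the four stratification factors: it is valid, but adjusting for them would align analysis with design and gain a little efficiency

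*Protocol article*

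**What the plan says.** **Randomisation.** The Randomization section lists the factors: "Patients are stratified for anticoagulation therapy (yes vs. no), extended lymphadenectomy (yes vs. no), diabetes mellitus (yes vs. no), and the surgeon performing the procedure". It adds that "blocking within the strata will be performed". The stated purpose is to stop factors that may influence lymphocele formation from being unbalanced between arms.

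**Analysis.** Under Statistical methods, Outcomes, the only test given for a binary endpoint, and so for the primary endpoint, is unadjusted: "We will use chi-squared test for binary outcomes". The same section says "Multivariable analyses will be based on logistic regression for binary outcomes". Additional analyses then states: "A sensitivity analysis of the primary endpoint will adjust for the pre-randomization variables which might reasonably be expected to be predictive of outcomes". These variables are not listed, and the text does not say that they are the stratification factors.

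**The anticoagulation stratum.** It is defined twice. Randomization records it as yes or no. Concomitant care says that some patients need therapeutic anticoagulation and all others receive prophylactic heparin, and concludes: "Hence, we will stratify for therapeutic or prophylactic anticoagulatory therapy".

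**The concern.** Blocking within strata forces the arms to be similar on the stratification factors. If those factors predict the outcome, the true variance of the difference in proportions is smaller than the pooled binomial variance used by the chi-squared test. The test is then somewhat conservative, and some of the precision that stratification provides is not used. With few expected events, even a small loss deserves attention.

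The planned logistic regression does not settle the matter. Neither the covariates nor the type of test is named, and with sparse events the type of test matters more than the adjustment itself.

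The anticoagulation wording matters because the factor enters the randomisation form and would enter any adjusted model. If every patient receives some anticoagulant, a yes/no answer can be read in two ways.

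**Working it through.** **1. The plan's own figure.** Inputs from Sample size: "we assume a rate of symptomatic lymphoceles of 10% for the control group which can be reduced to 2% for the PELYCAN group", one-sided α 0.025, power 80%. The pooled two-proportion formula without covariates is

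n per arm = [z₀.₉₇₅√(2p̄q̄) + z₀.₈₀√(p₁q₁ + p₂q₂)]² / (p₁ − p₂)²

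with p̄ = 0.06:

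[1.960 × √0.1128 + 0.8416 × √0.1096]² / 0.08² = (0.6583 + 0.2786)² / 0.0064 = 137.2, so 138.

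The plan has 141, which is within 3%. Then 282 / 0.94 = 300. The sizing therefore agrees with an unadjusted test. At 141 per arm the same formula gives 81.1% power. Summing the two binomial distributions over all tables that the chi-squared test rejects gives 84.6%. That explains why the simulated powers below lie near 85%.

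**2. Expected events.** Final analysis: 141 × 0.10 + 141 × 0.02 = 14.1 + 2.8 = 16.9. Interim (120 patients): 60 × 0.10 + 60 × 0.02 = 7.2. Strata: 2 × 2 × 2 = 8 per surgeon. With 4 surgeons (assumed) there are 32 strata, or 282 / 32 = 8.8 patients and 16.9 / 32 = 0.5 events per stratum.

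**3. Three binary factors as main effects, score test.** Simulation with 282 patients, one-sided 0.025 and no interim look. Assumptions not in the protocol: 4 surgeons, factor prevalences 15%, 40% and 15%, blocks of 4, and the same odds ratio (OR) for each factor.

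| Factor OR | Power, chi-squared | Power, score | Error, chi-squared | Error, score |
|---|---|---|---|---|
| 1 | 84.6% | 84.8% | 2.5% | 2.6% |
| 2 | 84.8% | 85.5% | 2.3% | 2.4% |
| 3 | 85.5% | 87.0% | 2.0% | 2.5% |

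The gains are 0.2, 0.7 and 1.5 points. Independent repeats gave 0.1, 0.4 and 1.2 points (6,000 runs) and 0.1, 1.0 and 1.4 points (5,000 runs). In the 6,000-run repeat the score test's error was 2.6%, 2.9% and 2.5%, against 2.5%, 2.6% and 2.2% for chi-squared (standard error 0.2).

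**4. The form of adjustment.** Power with surgeon also in the model (4 surgeons, 10,000 runs, 10% versus 2%; a surgeon effect is included at OR 2 and 3):

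| Factor OR | Chi-squared | Score | CMH, all strata | Wald |
|---|---|---|---|---|
| 1 | 83.9% | 84.2% | 82.7% | 75.5% |
| 2 | 85.4% | 86.3% | 83.4% | 77.7% |
| 3 | 84.8% | 86.7% | 83.0% | 78.4% |

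Relative to chi-squared, score gains 0.4 to 1.9 points, CMH loses 1.2 to 2.0 and Wald loses 6.4 to 8.4. The logistic fit failed or separated in 15 to 22% of these runs. At OR 3 the error was 2.17% for chi-squared and 2.67% for the score test with surgeon. Without surgeon, a three-factor Wald test still lost power: 76.3%, 77.0% and 77.4%, against 84.9%, 85.0% and 84.5% for chi-squared in the same runs. That is a loss of 8.6, 8.0 and 7.1 points.

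**5. The interim.** At 120 patients, one arm or one factor level had no events in 44 to 66% of simulated datasets. The adjusted score test lost no power there, but its error was about 2.5 to 3.0%. At OR 3 one set of runs gave 3.0%, against 2.4% unadjusted (standard error 0.2).

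**6. The anticoagulation stratum.** Taken literally, the yes/no form gives yes for everyone, because Concomitant care has all patients on either therapeutic or prophylactic treatment. If yes is shorthand for therapeutic, the two sections agree. The text does not say which was used.

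**The case against.** The strongest case for the plan is that the chi-squared test is sound and adjustment is already provided for. Its error is at or below nominal throughout, and the sample size was derived for it. The background calls the evidence for most of the risk factors debated; if their odds ratios are near 1, adjustment gains almost nothing. At the interim, about 7 events make a simple test a reasonable choice. The exact covariate list is usual content for a statistical analysis plan. All of this stands, and it limits the point to an improvement.

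Three stronger readings are tempting, and the documents do not support them.

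- *The p value is wrong because it ignores the stratification.* It is not. The departure is at most mildly conservative, and the repeat runs do not show the adjusted test to be clearly better calibrated.
- *Adjustment is free power.* It is not. Two of the three adjusted tests tried lose power, and the interim error can run slightly high.
- *The yes/no wording makes the anticoagulation stratum meaningless.* That follows only if yes does not mean therapeutic, which Concomitant care suggests it does.

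Timing is a fair objection. The Recruitment section reports 119 consenting patients six months after recruitment began. The first randomisation was in September 2019, follow-up lasts six months and the protocol version is dated October 2020. The interim data may therefore already have been close to complete.

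Two things survive. The protocol itself fixes an unadjusted primary test after a four-factor stratified randomisation, and the adjusted analysis is not tied to those factors. The two descriptions of the anticoagulation stratum also differ.

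**Conclusion.** The point holds as a small efficiency and alignment improvement. The primary test does not reflect the randomisation, but it is valid, with one-sided error of about 2.0 to 2.5%. A three-factor score test is expected to gain 0 to about 2 power points at 10% versus 2%. That figure rests on assumed prevalences, odds ratios of 1 to 3, 4 surgeons, blocks of 4 and no interim look. Runs with 3 and 5 surgeons showed the same pattern for the tests that include surgeon.

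The most practical consequence concerns the adjusted analysis already planned. If it is reported as a Wald test, it could disagree with the primary result only because it has about 6 to 9 points less power.

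The anticoagulation wording is a separate inconsistency, to be resolved by checking what was recorded.

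**What to change.** 1. **Primary test.** Use the score test of treatment in a logistic model with anticoagulation, extended lymphadenectomy and diabetes as main effects. Name penalised likelihood as the fallback under separation; its operating characteristics were not simulated here and should be checked first.
2. **Sensitivity analyses.** Keep the unadjusted chi-squared test as the sensitivity analysis, and add surgeon only in a further one. State that the covariates under Additional analyses are the stratification factors. Avoid Wald tests and fully crossed CMH.
3. **Interim.** Allow the unadjusted test or an exact stratified test at 120 patients. Write down which test applies at each look, together with the p-value adjustment for the adaptive design.
4. **Timing.** Fix all of this before anyone sees unblinded interim data. If they have been seen, leave chi-squared as primary and name only the covariates and test of the sensitivity analysis.
5. **Anticoagulation stratum.** Reconcile Concomitant care with Randomization, confirm the coding used for patients already randomised (140 at protocol submission), and use that same definition in the analysis.

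The cost is protocol wording and a check of the randomisation records. The three binary factors and surgeon are already captured at randomisation, so no new data are needed. The statistical price is the slightly raised interim error if the adjusted test is used there.

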#### Participant timeline

During the PELYCAN trial (Fig. 4), every patient, who will receive RARP will be handed patient, who will receive RARP will be handed out the patient education and informed consent materials, when he registers for his appointment with our secretary and trained research nurses. All participants receive the same information sheet and consent form. It is highlighted that the agreement to participate is voluntary. The patient is given enough time to study the participant education. All members of the admission team (nurses and admitting doctors) have been trained in detail about the study and its content. The admitting doctors are specialists only. All patients will be seen and screened by the admission doctor at their pre-admission appointment at our outpatient clinic. Their current medication is assessed and the QLQ-C30 (EORTC) is completed by the patients. All patients, who decide about receiving the operation on their own, are determined to have sufficient decisional capacity regarding trial participation. Participants not being able to speak or read German and patients with previous history of head injury, dementia, or psychiatric disease and patients lacking the decisional capacity for the operation itself are considered to lack the decisional capacity for study participation. If eligible, patients are invited to participate in the trial and informed consent is obtained. The patients’ questions will be addressed carefully.

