**Fig. 4 Fig4:**
[figure not shown]
PELYCAN-trial flow diagram according to SPIRIT [33]

Patients will receive ultrasonography examination at the day of discharge. The assessor will be the responsible ward doctor, who is blinded to group assignment. The main outcome interests are the occurrence of symptomatic lymphoceles. Patients will be assessed using questionnaires, which will be sent via email or post 6 months postoperatively. For data completion, we will also contact the patients’ outpatient urologists, who are responsible for the follow-up and medical/oncological aftercare. This increases the validity of our data. The questionnaires will be designed with questions which only can be answered dichotomously (“yes” or “no”). By that, we assure reproducible data. Additionally, patients will be sent the same quality of life (QoL) questionnaire they already have answered preoperatively (QLQ-C30, EORTC). Please refer to Table 1 for the detailed SPIRIT participant timeline.

**Table 1 Tab1:** Participant timeline (adapted from the original table)

Timepoint	Study period						
	Staff members	−t1	0	t1.1	t1.2	t2	t3
Activity/assessment		Screening and consent	Allocation	Surgery	Peritoneal flap	Day of discharge	6-month follow-up

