**Assessments**							
Pre-existing medical conditions	AD	x					
Medication	AD	x				x	
Abdominal ultrasound	AD	x				x	
Quality of life (QLQ-C30, EORTC)	AD, PU	x					x
Lymphocele (symptomatic/asymptomatic)	WD, PU					x	x
Lymphocele symptoms	WD, PU					x	x
Lymphedema/erysipelas	PU						x
Rehospitalization	PU						x

*Enroll* enrolment, *INT* intervention, *SC* study coordinator, *AD* admission doctor, *OS* operating surgeon, *WD* ward doctor, *PU* private urologist

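### The only between-arm comparison named for the QLQ-C30 is an unadjusted t test; adjusting for the baseline score already collected would gain precision at no data cost

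*Protocol article*

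**What the plan says.** Quality of life by QLQ-C30 is a listed secondary endpoint (protocol article, Secondary outcome measures). It is measured twice. At the pre-admission visit: "Their current medication is assessed and the QLQ-C30 (EORTC) is completed by the patients" (Participant timeline). At 6 months: "patients will be sent the same quality of life (QoL) questionnaire they already have answered preoperatively" (text following Fig. 4). Table 1 marks the instrument at screening and at the 6-month follow-up.

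The Outcomes section under Statistical methods assigns the tests: chi-squared for binary outcomes and a t "test for continuous outcomes". The same paragraph adds: "Multivariable analyses will be based on logistic regression for binary outcomes and linear regression for continuous". That sentence names no outcome and no covariates.

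Adjustment for pre-randomisation variables is attached to one outcome only (Additional analyses): "A sensitivity analysis of the primary endpoint will adjust for the pre-randomization variables which might reasonably be expected to be predictive of outcomes". The primary endpoint is binary.

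On the standing of the remaining analyses, the Outcomes section says: "All other analyses will be exploratory with 2-sided" p values at 0.05. It adds a power of 80% but gives no effect size for the QLQ-C30.

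**The concern.** A patient's quality-of-life score before surgery usually predicts part of the score at 6 months. A two-sample t test on the 6-month score leaves that predictable part in the residual variance. A t test on change removes some of it, but with the slope on baseline fixed at 1, which can add noise when the correlation is low. A regression on arm and baseline score estimates the slope from the data.

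What is at stake is the width of the interval for the quality-of-life difference. Under the planning rates of 10% and 2% for symptomatic lymphocele, only a small share of patients would differ between arms on that event. Any resulting shift in mean quality of life may therefore be small, and precision is worth having. Leaving open whether the 6-month score or the change is tested also leaves a choice that could be made after the data are seen.

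**Working it through.** **The plan's own figure.** The Sample size section gives 141 per arm for 10% against 2%, one-sided alpha 0.025 and 80% power. The pooled formula without continuity correction is

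n = [1.960·√(2·0.06·0.94) + 0.842·√(0.10·0.90 + 0.02·0.98)]² / 0.08² = 138 per arm.

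This is within 3% of 141, and power at 141 per arm is 81.1%. The total of 282 / (1 − 0.06) = 300 also reproduces. The calculation serves the primary endpoint. No sample size or effect size is stated for the QLQ-C30, so 141 per arm is used below only as the number of patients available.

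**Inputs for the QLQ-C30 comparison**
- n = 141 per arm with both questionnaires (Sample size section, after the drop-out allowance).
- Two-sided alpha 0.05 (Statistical methods, Outcomes).
- r, the correlation between baseline and 6-month score within arm. The documents do not give it; 0.3 to 0.7 is assumed.
- Equal SD at baseline and 6 months (assumed, for the change-score column).

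**Formulas.** Large-sample variance of the arm difference, relative to a t test on the 6-month score:
- t test on the 6-month score: 1
- t test on change: 2 − 2r
- ANCOVA: 1 − r²

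Change minus ANCOVA is (2 − 2r) − (1 − r²) = (1 − r)², which is never negative. If the baseline SD is k times the 6-month SD, the gap is (k² − 2rk + 1) − (1 − r²) = (k − r)², again never negative. ANCOVA is therefore at least as precise as either form of t test.

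Detectable difference at 80% power, in SD of the 6-month score: (1.960 + 0.842)·√(2/141 × relative variance). For the t test on the 6-month score this is 2.802 × 0.1191 = 0.334 SD.

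| r | ANCOVA relative variance | Reduction against 6-month t test | Change-score relative variance | Detectable difference, ANCOVA (SD) | ANCOVA power at 0.334 SD |
|---|---|---|---|---|---|
| 0.3 | 0.91 | 9% | 1.40 | 0.318 | 83.6% |
| 0.4 | 0.84 | 16% | 1.20 | 0.306 | 86.4% |
| 0.5 | 0.75 | 25% | 1.00 | 0.289 | 89.9% |
| 0.6 | 0.64 | 36% | 0.80 | 0.267 | 93.8% |
| 0.7 | 0.51 | 49% | 0.60 | 0.238 | 97.5% |

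At r = 0.5, 282 patients analysed with the baseline are worth 282 / 0.75 = 376 analysed by a t test on the 6-month score.

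If the t test is on change, the ANCOVA variance is (1 − r²)/(2 − 2r) = (1 + r)/2 of it: 0.65 at r = 0.3, 0.75 at r = 0.5 and 0.85 at r = 0.7. The reduction on that reading is 35% down to 15%. Below r = 0.5, a t test on change is less precise than ignoring the baseline.

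The variance ratios do not depend on n, so they would also hold after a sample size recalculation.

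**The case against.** A reader might infer that the plan discards the baseline score. The documents do not support that. The t test could be on change, which uses the baseline, and the planned linear regression for continuous outcomes could include it. The supportable statement is narrower: the only comparison named is unadjusted, and the role of the baseline is not specified.

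It can also be said that the model for one secondary scale belongs in the analysis plan, which is not shown. That would answer a complaint about missing detail. Here, however, the protocol does name a test for this class of outcome, and a more precise one is available from data it already collects. The regression sentence assigns nothing to the QLQ-C30, so it does not settle the matter.

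Three further objections stand and limit the point:
- In a randomised trial the unadjusted t test is valid and unbiased. Chance baseline imbalance is covered by its standard error and is not a bias.
- The QLQ-C30 is one of several exploratory secondary outcomes with no stated target difference.
- The gain depends on an unknown correlation. At r = 0.3 the detectable difference moves only from 0.334 to 0.318 SD.

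Nor should full return of the 6-month form be assumed: it goes out by email or post, and the protocol foresees some non-return.

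**Conclusion.** The point holds as a minor, free improvement. Baseline adjustment of the QLQ-C30 would reduce the variance by r² against a t test on the 6-month score, that is 9% to 49% for r between 0.3 and 0.7. It would do at least as well as a t test on change at any correlation. With 141 per arm, the difference detectable at 80% power would fall from 0.334 SD to between 0.318 and 0.238 SD.

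These sizes rest on the assumed correlation, on 141 per arm returning both forms and, for the change-score figures, on equal SDs at the two times. The direction does not depend on those assumptions. The primary test, the sample size and the interim analysis are untouched.

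**What to change.** In Statistical methods, Outcomes, state that each QLQ-C30 scale at 6 months will be compared by linear regression on arm, the same scale's baseline score and the randomisation factors (anticoagulation, extended lymphadenectomy, diabetes, surgeon). Report the adjusted mean difference with its 95% CI. Keep the t test for continuous outcomes without a baseline measurement, such as operating time, blood loss and length of stay.

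The cost is one sentence. It needs no further patients, visits or data, and linear regression is already among the planned methods. Writing it down before the arms are compared also settles the choice between 6-month score and change.
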